## Abstract

**Background:**

Endometrial carcinoma is the most common gynaecologic malignancy in industrialised countries and the incidence is still rising. Primary treatment is based on preoperative risk classification and consists in most cases of hysterectomy with bilateral salpingo-oophorectomy. In patients with serous and clear cell histology a complete surgical staging is mandatory. However, in routine clinical practice final histology regularly does not correspond with the preoperative histological diagnosis. This results in both over and under treatment.

**Methods/Design:**

The aim of this multicentre, prospective cohort study is to select a panel of prognostic biomarkers to improve preoperative diagnosis of endometrial carcinoma in order to identify those patients that need extended surgery and/or additional treatment. Additionally, we will determine whether incorporation of cervical cytology and comorbidity could improve this preoperative risk classification. All patients treated for endometrial carcinoma in the participating hospitals from September 2011 till December 2013 are included. Patient characteristics, as well as comorbidity are registered. Patients without preoperative histology, history of hysterectomy and/or endometrial carcinoma or no surgical treatment including hysterectomy are excluded. The preoperative histology and final pathology will be reviewed and compared by expert pathologists. Additional immunohistochemical analysis of IMP3, p53, ER, PR, MLH1, PTEN, beta-catenin, p16, Ki-67, stathmin, ARID1A and L1CAM will be performed. Preoperative histology will be compared with the final pathology results. Follow-up will be at least 24 months to determine risk factors for recurrence and outcome.

**Discussion:**

This study is designed to improve surgical treatment of endometrial carcinoma patients. A total of 432 endometrial carcinoma patients were enrolled between 2011 and 2013. Follow-up will be completed in 2015. Preoperative histology will be evaluated systematically and background endometrium will be classified. This is the first study incorporating immunohistochemistry, cervical cytology and comorbidity to define the optimal panel of prognostic biomarkers that contribute in clinical decision making in the management of endometrial carcinoma.

**Trial registration:**

Netherlands Trial Register number NTR3503

## Background

Endometrial carcinoma (EC) is the most common gynaecologic malignancy in the United States with approximately 52,630 diagnosed cases annually [1]. In the Netherlands the incidence is about 1900 women, with a mortality rate of 480 [2]. The incidence is still rising due to increased life expectancy and obesity as important risk factor [3]. Although the majority of patients are diagnosed at an early stage with a favourable prognosis, still around 20 % of patients die from the disease [4]. ECs are staged according to the 2009 Fédération Internationale de Gynécologie et d’Obstétrique (FIGO) classification. ECs are divided into two types. The majority of ECs are classified as type I and are related to unopposed oestrogenic stimulation resulting from obesity or exogenous hormone use and originate from hyperplastic endometrium. This tumour type is associated with early stage disease, endometrioid histology, and a favourable outcome after surgery [5]. In contrast, type II carcinomas are unrelated to oestrogenic stimulation and arise in a background of atrophic endometrium. Type II carcinomas are associated with advanced stage, high grade, non-endometrioid histology, and an overall a poor prognosis [5]. A recent study suggests the existence of a third type of EC characterised by low grade endometrioid endometrial carcinoma (EEC) and a background of atrophic endometrium [6]. This third type of EC may have a poorer prognosis when compared to type I carcinomas [6]. However, recently published data of The Cancer Genome Atlas (TCGA) Research Network, identified four subgroups of EC based on molecular classifiers such as *TP53*, *PTEN* and microsatellite instability [7]. This supports the need for adjusting the currently used classification.

### Primary treatment

Primary treatment is currently based on preoperative risk classification and consists of hysterectomy with bilateral salpingo-oophorectomy. In uterine papillary serous carcinoma (UPSC) and clear cell carcinoma (CCC) a complete surgical staging is mandatory because of the high risk of extra-uterine disease [8–10]. Although the presence of lymph node metastasis is an unfavourable predictor for disease specific survival, data of Kwon et al. demonstrated that high-risk uterine factors including high grade tumour type, deep myometrial invasion, and cervical stromal involvement are more significant determinants of survival in EC than pelvic-node status [11]. The current study focuses on diagnosis and preoperative risk assessment of patients with EC.

### Preoperative diagnosis

During the last decades dilatation and curettage (D&C) has been replaced by minimally invasive techniques for endometrial sampling in an outpatient setting. The amount of tissue obtained from endometrial sampling is relatively small and there can be different subtypes of EC in one tumour, making routine histological discrimination between EEC and a high grade, UPSC or CCC difficult. Moreover, in 30 % the amount of tissue obtained with outpatient endometrial sampling is insufficient for diagnosis [12]. Previous studies found discrepancy percentages between 15 and 40 %, including both grade and histological subtype [13–17]. When preoperative diagnosis was based on D&C or endometrial sampling, a preoperative diagnosis of grade 1 was concordant with the final diagnosis in 85 % of cases. However, high grade lesions were more frequently underestimated by endometrial sampling compared to D&C [18].

### Immunohistochemical analysis in preoperative endometrial sampling

Identification of a panel of immunohistochemical (IHC) markers may be helpful to establish a reliable preoperative risk classification. A brief summary of the selected markers that will be tested is given in Table 1. P53 immunopositivity is associated with non-endometrioid EC [19]. Negative IHC for oestrogen and progesterone receptors can predict lymph node metastasis and is associated with decreased survival [20]. Double negative hormone receptor status and p53 immunopositivity correlates with lymph node metastasis, high FIGO stage, non-endometrioid histology, high grade and poor prognosis [20]. Insulin-like growth factor II messenger RNA-binding protein 3 (IMP3) is a foetal protein not expressed in normal adult tissues. This oncoprotein plays an important role in tumour growth, migration and invasion. IMP3 could contribute to the preoperative identification of type II tumours, since it is more frequently expressed in UPSC and CCC when compared to EEC (resp. 78 %, 57 % and 15 %) [21]. A recent study showed that L1CAM is the best predicting prognostic factor in FIGO stage I, type I EC and superior to the standard used multifactor risk score (myometrial invasion, tumour grade and lymph space or vascular invasion) [22]. L1CAM immunohistochemistry can improve the identification of patients at risk for recurrent disease. However, all the mentioned biomarkers are lacking validation on pre-operative histological samples and are based on singles studies. Further research has to validate these promising results.

**Table 1 Tab1:** Immunohistochemical analysis

Immunohistochemical marker		Results	Ref.
IMP3	Insulin-like growth factor II mRNA-binding protein 3	IMP3 is more frequently expressed in UPSC and CCC than in EEC (resp. 78 %, 57 % and 15 % of the tumours were positive).	[21]
P53		P53 is more expressed in non-endometrioid endometrial carcinomas than in EEC. Expression is also related to higher tumour grade.	[19]
ER and PR	Oestrogen and progesterone receptor	Negative receptors were associated with lymph node metastasis and decreased survival. ER and PR expression is lower in non-endometrioid endometrial carcinomas than in EEC.	[20, 34]
MLH1	MutL homolog 1	Loss of expression of mismatch repair proteins is seen in high grade EEC and not in UPSC and CCC. Loss of MLH1 expression is associated with longer survival.	[35, 36]
PTEN	Phosphatase and tensin homologue	PTEN positivity is more frequently found in UPSC than EEC.	[19]
Beta-catenin		Positive beta-catenin expression is associated with decreased stage, decreased grade and negative lymph node status	[37]
P16		Loss of p16 expression is significantly correlated with high FIGO stage and serous and clear cell histological subtype.	[38]
Ki-67		Higher Ki-67 expression is associated with higher tumour grade. UPSC and CCC show higher Ki-67 proliferation index than EEC.	[34]
Stathmin		Stathmin overexpression was associated with non-endometrioid histology, high grade and poor disease-specific survival.	[39]
ARID1A	AT-rich interactive domain 1A gene	Loss of ARID1A expression is significantly more frequent in high grade EEC compared to UPSC.	[40]
L1CAM	L1 cell adhesion molecule	L1CAM is associated with higher grade and non-endometrioid histology. Moreover, L1CAM positive EC have statistical significant poorer disease-free survival and overall survival.	[22]

*UPSC* = Uterine papillary serous carcinoma; *CCC* = Clear Cell Carcinoma; *EEC* = Endometrioid endometrial carcinoma; *EC* = endometrial carcinoma; *FIGO* = Fédération Internationale de Gynécologie et d’Obstétrique

### Preoperative diagnosis of EC in cervical cytology

The presence of endometrial cells in cervical cytology in postmenopausal women is strongly associated with endometrial pathology [23]. Abnormal cervical cytology is associated with extra-uterine disease in patients with UPSC and with cervical involvement in patients with EEC [24]. A combination of preoperative cervical cytology with endometrial sampling might better predict final histology and risk for extended disease. In a study of Kinde et al. DNA was extracted from cervical smears to detect genetic disorders present in EC [25]. The mutation profile found in the primary tumour was found in all of the cervical smears [25]. These results indicate that cervical cytology might be a reliable and minimal invasive source of material for detection of EC.

### Comorbidity and EC

The impact of comorbidity on cancer outcome has been underestimated for a long time. Recently published data demonstrated that EC patients with cardiovascular disease, previous malignancy and diabetes have a significantly decreased survival of 15–17 % compared to patients without comorbidity [26]. Additionally, patients with diabetes and EC have more comorbidities, higher body mass index (BMI) and higher FIGO stage, compared to those without diabetes [27]. There is also a significant increase in the risk of EC-specific mortality among women with diabetes [28]. Although obesity is a risk factor for development of EC, obesity seems not related to overall survival [29]. Yet, comorbidity has demonstrated to influence the outcome in EC [30].

In summary, the main challenging issue concerning clinical management of EC patients is underscored by the discordance between the preoperative risk classification of the tumour and the final surgical pathology. At the moment a subgroup of patients needs either a secondary surgical staging procedure or additional chemotherapy and/or radiation therapy. With the current study we want to select a panel of the most accurate biomarkers that can be used in daily practice for preoperative diagnosis of EC. This will aid in improving the concordance between preoperative and final histological diagnosis and thus prevent over and under treatment. Incorporating cervical cytology and comorbidity could potentially improve a proper risk classification in EC patients.

## Methods/Design

### Objective

#### Primary objective

To determine whether standardized evaluation of endometrial biopsies with additional immunohistochemical analysis, could predict final histological type, tumour grade and stage.

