### Study design

Multicentre, prospective cohort study in nine hospitals in the Netherlands. From September 1st 2011 till December 1st 2013 all patients treated for EC in participating hospitals are included. Patients without preoperative histology, history of hysterectomy and/or endometrial carcinoma or no surgical treatment including hysterectomy are excluded. Patient characteristics, as well as comorbidity (Charlson index), BMI, family history of hereditary syndromes (BRCA1/2, Lynch syndrome), postmenopausal status and parity are registered. Based on the present comorbidities, all patients are assigned a comorbidity score based on the Age-Adjusted Comorbidity-index as described by Charlson et al. [31], with EC being excluded from the scoring. Treatment and final pathological diagnosis are registered as well as occurrence of recurrent disease during at least 24 months follow-up.

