## Discussion

A total of 432 EC patients from nine hospitals were collected between September 2011 and December 2013. The inclusion of patients has finished and we are now analysing the data. Follow-up will be completed in December 2015. The various histological subtypes of EC are all represented in this study group with 86 % EEC, 8 % UPSC and 2 % CCC based on hysterectomy evaluation. This is in line with percentages reported in the Netherlands Cancer Registry [32]. Clinicopathological characteristics are shown in Table 2. Atypical hyperplasia is diagnosed in 13 % of the preoperative endometrial samples, where final diagnosis on hysterectomy was EC.

**Table 2 Tab2:** Clinicopathological characteristics of 432 women with endometrial carcinoma. Values are presented as median (range) or number (%)

Characteristics		
Age at primary surgery, years	66	(41–90)
Pre-operative histology^a^		
Office endometrial biopsy	311	(72.0)
Hysteroscopic biopsy	128	(29.6)
Curettage	75	(17.4)
Histological subtype^b^		
Endometrioid	370	(85.6)
Serous papillary	33	(7.6)
Clear cell	9	(2.1)
Mucinous adenocarcinoma	2	(0.5)
Carcinosarcoma	18	(4.2)
Histological grade^b^		
1	193	(44.7)
2	127	(29.4)
3	112	(25.9)
FIGO 2009 stage		
I	362	(83.8)
II	27	(6.3)
III	35	(8.1)
IV	8	(1.9)

^a^ 82 patients have more than one pre-operative histological sample

^b^ Unrevised classification based on hysterectomy specimen

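### Final stage is a primary target, but the search for nodal disease probably depends on the preoperative histology, so marker–stage associations in all patients would be inflated by an unknown amount

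*Protocol article*

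**What the plan says.** The Primary objective has three targets: the biopsy with added immunohistochemistry is to show whether it "could predict final histological type, tumour grade and stage". Stage stands beside type and grade without qualification.

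The section Primary treatment describes how surgery is chosen: "Primary treatment is currently based on preoperative risk classification and consists of hysterectomy with bilateral salpingo-oophorectomy". For uterine papillary serous and clear cell carcinoma it adds that "a complete surgical staging is mandatory because of the high risk of extra-uterine disease". The Abstract repeats the rule: "In patients with serous and clear cell histology a complete surgical staging is mandatory".

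The Background also mentions a later route to staging, in its summary of discordance between preoperative classification and final pathology: "At the moment a subgroup of patients needs either a secondary surgical staging procedure or additional chemotherapy and/or radiation therapy".

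Study design sets no condition on nodal assessment. The surgical exclusion reads "no surgical treatment including hysterectomy are excluded", so a hysterectomy is enough for entry. Treatment and final pathological diagnosis are registered.

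Under Statistical analysis, biopsy and curettage results are compared with final pathology, and univariate and multivariate analyses test whether the markers help predict it. No distinction is drawn by extent of surgery.

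**The concern.** Type and grade are read from a specimen that every patient provides. The nodal part of stage is not, because it can be established only where nodes were examined. By the article's own account, the preoperative classification helps determine who has that examination, and preoperative tumour type and grade are among the features evaluated on the biopsy. Several markers were chosen because they separate serous and clear cell from endometrioid tumours. The article gives IMP3 positivity as 78 %, 57 % and 15 % in serous, clear cell and endometrioid carcinoma.

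This is differential verification: the chance that the outcome is detected depends on the predictor. If unexamined nodes count as negative, a marker of serous or clear cell histology will appear to predict advanced stage partly because its carriers were searched more thoroughly. Nodal disease missed in marker-negative patients drops out of the denominator of sensitivity, which is then overstated. Both errors favour the markers. Blinding the pathologists does not help, because the bias enters when the operation is chosen.

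**Working it through.** **What the documents supply.** No staging rate, nodal rate or coding rule for unexamined nodes is given, so there is no figure of the plan's own to reproduce on this point. Table 2 gives the setting.

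- FIGO stages: 362 + 27 + 35 + 8 = 432, so every patient has a stage.
- Stage III–IV: 35 + 8 = 43, and 43/432 = 10.0 %.
- Final serous plus clear cell: 33 + 9 = 42, and 42/432 = 9.7 %. For the other 390 (90.3 %) the article states no mandatory complete staging. These are unrevised final diagnoses, so they only approximate the preoperative split.

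**Illustration 1: assumed staging rates by marker status.** Let true nodal disease be p = 10 % whatever the marker (true odds ratio 1.0). Let a and b be the shares of marker-positive and marker-negative patients who are staged, and let unexamined nodes count as negative. The recorded rates are then p·a and p·b, and the odds ratio is [pa/(1 − pa)] / [pb/(1 − pb)].

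| Staged, marker + / − | Recorded nodal disease | Spurious odds ratio |
|---|---|---|
| 60 % / 15 % | 6.0 % / 1.5 % | 0.0638/0.0152 = 4.19 |
| 70 % / 30 % | 7.0 % / 3.0 % | 0.0753/0.0309 = 2.43 |
| 40 % / 20 % | 4.0 % / 2.0 % | 0.0417/0.0204 = 2.04 |

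For sensitivity, suppose also that 20 % of patients are marker-positive. True sensitivity is then 20 %, since the marker is uninformative. With 60 %/15 % staging, recorded sensitivity is 0.20 × 0.06 / (0.20 × 0.06 + 0.80 × 0.015) = 0.012/0.024 = 50 %. With 40 %/20 % it is 0.008/(0.008 + 0.016) = 33 %.

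**Illustration 2: tied to the one marker the article quantifies.** Apply the IMP3 percentages to the 33 serous, 9 clear cell and 370 endometrioid tumours in Table 2.

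- IMP3-positive: 25.7 + 5.1 + 55.5 = 86.4, of which 30.9 (36 %) are serous or clear cell.
- IMP3-negative: 412 − 86.4 = 325.6, of which 42 − 30.9 = 11.1 (3.4 %) are serous or clear cell.

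Assume that all serous and clear cell patients are staged, together with a share q of the endometrioid patients. Then a = 0.357 + 0.643q and b = 0.034 + 0.966q. With p = 10 % again:

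| q | a | b | Spurious odds ratio |
|---|---|---|---|
| 12 % | 43 % | 15 % | 3.0 |
| 25 % | 52 % | 28 % | 1.9 |
| 50 % | 68 % | 52 % | 1.3 |
| 100 % | 100 % | 100 % | 1.0 |

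**Illustration 3: preoperative histology itself as the predictor.** If all patients with a serous or clear cell biopsy are staged, and a share s of the others, equal true rates of 10 % give odds ratios of 11.0, 4.3, 2.1 and 1.4 for s = 10 %, 25 %, 50 % and 75 %. For s = 25 %, this is (0.10/0.90)/(0.025/0.975) = 4.3.

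The direction is the same throughout. The size depends almost entirely on how many patients outside the serous and clear cell group had nodes assessed.

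**The case against.** The strongest reply is that the article does not establish how uneven the staging was. Most of this stands.

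- A reader might infer that complete staging is done only for serous and clear cell biopsies, so that the predictors alone settle who can be found node-positive. The article says mandatory, not exclusive. Other patients may have been staged, and it mentions a secondary staging procedure for a subgroup. That procedure makes assessment less uneven, but nothing suggests that it makes it uniform.
- A reader might infer that patients without nodal assessment are recorded as stage I–II by default. Table 2 shows no unstaged category, but nothing says how unexamined nodes were coded.
- Not all stage III–IV disease depends on complete staging. Salpingo-oophorectomy is part of standard treatment, so adnexal spread can be seen without it. The 43 stage III–IV cases are not broken down by how they were found.
- The Table 2 footnote "Unrevised classification based on hysterectomy specimen" is attached to subtype and grade, not to stage, and lends no support here.
- Stage is one target of three. The sample size rests on high risk carcinoma, and the Discussion puts the focus on histological type and tumour grade.
- The odds ratios above are crude. The nine variables in the sample-size section (age, two terms for grade, six markers) would adjust for grade and so might absorb part of the bias. Preoperative histological type is not among them.

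It can also be said that the handling of unstaged patients belongs in a full protocol or analysis plan that is not shown. That would answer a complaint about missing detail. The point here is different: the article makes stage a primary target in all patients and itself describes a treatment pathway in which its ascertainment is tied to the predictor.

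**Conclusion.** The concern holds for the nodal part of stage, and for extra-uterine disease that only complete staging would reveal. If the comparison is run in all patients as described, associations between serous- or clear-cell-related markers and advanced stage, and the markers' sensitivity for it, would be biased upward.

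The size cannot be derived from the documents. With true nodal disease assumed to be 10 % regardless of marker and unexamined nodes counted as negative, spurious odds ratios of about 2.0 to 4.2 follow from staging of 40 % versus 20 % up to 60 % versus 15 %. If half or more of the remaining patients were staged, the bias for a marker like IMP3 would be modest (1.3 or less).

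Type, grade, myometrial invasion and cervical involvement are assessed in every hysterectomy specimen and are not affected in this way. The primary objective as a whole is therefore not undermined; one of its three targets needs a different analysis.

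**What to change.** Leave type and grade as they are and split the stage analysis in two.

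1. **Uterine components**: deep myometrial invasion and cervical stromal involvement, read in every hysterectomy specimen and analysed in all patients. The article itself cites data that "high-risk uterine factors including high grade tumour type, deep myometrial invasion, and cervical stromal involvement are more significant determinants of survival" than pelvic-node status. That ranking concerns survival, so it supports their relevance but does not make them a substitute for stage.
2. **Nodal disease**: analysed in patients whose nodes were assessed, with unassessed nodes treated as unknown, not negative.

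Report the extent of staging by preoperative histology and by marker status, so that readers can judge how uneven it was. Present overall FIGO stage in all patients only with that caveat. Inverse-probability weighting for having been staged is an optional sensitivity analysis, worth running only if enough low-risk patients were staged; otherwise the weights will be unstable.

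The cost is moderate. Treatment and final pathology are already registered, and no patient's care changes. The claim about stage becomes narrower, and the nodal analysis has fewer patients, who are themselves a selected group. Because inclusion has closed and analysis has begun, the split should be documented as a dated change, with the reason given.
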